## Abstract

**Background:**

Tutored laboratorial activities could be a manner of improving the competency development of students. However, its impact over conventional theoretical classes has not yet been tested. Additionally, different university contexts could influence this issue and should be explored.

**Objective:**

To assess the impact of a tutored theoretical-practical training for teaching undergraduate students to detect caries lesions as compared with theoretical teaching activities. The impact of these teaching/learning activities will be assessed in terms of efficacy, cost/benefit, retention of knowledge/acquired competences, and student acceptability.

**Methods:**

Sixteen centers (7 centers from Brazil and 9 centers from other countries throughout the world) are involved in the inclusion of subjects for this protocol. A randomized controlled study with parallel groups will be conducted. One group (control) will be exposed to a 60- to 90-minute conventional theoretical class and the other group (test) will be exposed to the same theoretical class and also a 90-minute laboratory class, including exercises and discussions based on the evaluation of a pool of images and extracted teeth. The mentioned outcomes will be evaluated immediately after the teaching activities and also in medium- and long-term analyses. To compare the long-term outcomes, students who enrolled in the university before the participating students will be interviewed for data collection and these data will be used as a control and compared with the trained group. This stage will be a nonrandomized phase of this study, nested in the main study. Appropriate statistical analysis will be performed according to the aims of this study. Variables related to the centers will also be analyzed and used to model adjustment as possible sources of variability among results.

**Results:**

This ongoing study is funded by a Brazilian national funding agency (CNPq- 400736/2014-4). We expect that the tutored theoretical-practical training will improve the undergraduate students’ performance in the detection of caries lesions and subsequent treatment decisions, mainly in terms of long-term retention of knowledge. Our hypothesis is that tutored theoretical-practical training is a more cost-effective option for teaching undergraduate students to detect caries lesions.

**Conclusions:**

If our hypothesis is confirmed, the use of laboratory training in conjunction with theoretical classes could be used as an educational strategy in Cariology to improve the development of undergraduate students’ skills in the detection of caries lesions and clinical decision-making.

## Introduction

### Background

There is an imminent demand to prepare dental professionals to not only possess knowledge, but also have developed skills to detect dental caries and make decisions about caries management based upon the current best scientific evidence [1]. Thus, an improved education in Cariology for dental undergraduate students as future practitioners is fundamental for adequate caries diagnoses [2].

A recent systematic review has pointed out that caries diagnosis is the topic within Cariology that has received the most concern in terms of developing training methodologies and/or education for undergraduate students [3]. This suggests not only the importance of the subject within the dental professional training, but also the difficulty involved in successfully preparing professionals to be able to perform this step in the dental clinic.

Although it may appear to be a simple step, the detection of caries lesions, as a part of the diagnosis process, involves several aspects that require not only knowledge about the subject, but also theoretical, clinical, and interpersonal skills. In this sense, practical training may be essential for the development of these specific skills [4]. The laboratory activities systematically provide opportunities for undergraduate students to experience different simulated situations covering a variety of circumstances that they should be able to solve in clinical practice. Moreover, practical training allows more interactivity between students and teachers and/or tutors in the teaching-learning process [5,6], besides providing rapid feedback on their performance [7]; thus, improving the educational outcome.

Several systems for caries detection have been used, to provide important information about the disease and also to guide professionals in making treatment decisions [8]. The International Caries Detection and Assessment System (ICDAS) is one of the options proposed to standardize this process internationally [9]. Although student performance in the detection of caries lesions using this system has already been assessed [10-12], these investigations were performed in small groups of students or in only 1 institutional center, reducing the external validity of these findings [13].

A preliminary study conducted at the University of São Paulo found that the tutored theoretical-practical training seems to improve the caries detection by undergraduate students using ICDAS [14]. However, it was not possible to assess the real impact of this active-learning methodology in the teaching of this field, which involves more time and costs, as compared with the theoretical activity alone. Furthermore, this effect may be dependent on different university contexts, mainly because caries diagnosis content has not been taught in the same way in different curricula. To the best of our knowledge, this is a pioneering multicenter study that aims to investigate the short- and long-term impact of the tutored theoretical-practical training for detecting caries lesions in undergraduate courses in comparison with theoretical activities.

### Objective

The aim of the present protocol will be to evaluate the effect of a tutored theoretical-practical training for teaching undergraduate students to detect caries lesions in comparison with theoretical teaching activities. The impact of these teaching/learning activities will be assessed in terms of efficacy, cost/benefit, retention of knowledge/acquired competences, and student acceptance.

## Methods

### Ethical Aspects

The Research Ethics Committee of all institutions involved previously approved this protocol. The participants will receive and sign an informed consent prior to their involvement in the research. For ethical reasons, the students allocated to the theoretical group will receive laboratory training at the end the outcome assessments. Participant confidentiality will be ensured using identification code numbers. Participant identifiable information will be stored in locked filing cabinets in a secure room.

### Study Design

A multicenter randomized controlled study with parallel groups will be conducted. One group (control) will be exposed to a 60- to 90-minute conventional theoretical class and the other group (test) will be exposed to the same theoretical class along with a 90-minute laboratory class, including exercises and discussions based on the evaluation of a pool of images and extracted teeth.

This study will involve 7 centers from Brazil and 9 centers from other countries throughout the world (Figure 1). The centers represent two distinct contexts: 1 coordinating center, a precursor in the development of the theoretical and laboratory activity that will be tested, while the other institutions represent those that will receive the proposal to develop the same activity with support provided by the precursor center. The inclusion of different centers aims to cover different regions and institutions with different profiles to increase the external validity of the study. As the coordinating center is in São Paulo, Brazil, 6 other institutions were invited to cover different parts of the country. Similarly, the other centers throughout the world are located in different regions, including Latin America (Colombia and Paraguay), Asia (Hong Kong), and Europe (Copenhagen, United Kingdom, and Portugal). Other centers may be optionally incorporated throughout the study, according to interest and judgment of necessity. The Initiatives for Undergraduate Students’ Training in Cariology is a collaborative group made up of all people involved in this study. The detailed roles of each member and respective affiliations are described in Multimedia Appendix 1.

### Training for Operationalization of the Study in Different Centers

The researchers responsible for the study in each center will participate in an initial joint meeting to clarify the methodology to be followed in the study. Training and collaboration of the participants from each center will be made in order to properly adapt the logistics needed for the study, considering the characteristics of each center. The research team will detect all particularities of each center, and a proposal for the implementation of the activity will be jointly developed by the coordinating center and each participating institution. In addition, the principal investigator will train the staff members that will apply the activity at each center.

### Preparation of the Material for Evaluations

The coordinating center will be responsible for organizing and/or assisting in the organization of the material to be used in the theoretical-practical training, including preparation of a pool of images and extracted teeth contemplating different stages of caries severity. The pool of images will be prepared and used in all centers. The teeth will be obtained from the Bank of Human Teeth located at each institution or similar donators of material for this purpose. A tutorial was developed to guide investigators from each center to prepare their samples aided by an investigator from the coordinating center.

**Figure 1 figure1:**
[figure not shown]
Mapping of the institutions involved in the study.

### Experimental Groups

Undergraduate students at the beginning (up to second or third year) and the end of the Dentistry course (last 2 years) will be included. All students will be invited to participate, but only those who consent to participate will be included. The classes will be randomly divided into 2 groups. The randomization will be made by a central allocation located in the coordinating center, by sending the list of students to be invited. All students will be randomized, even those that will not participate. These losses will be computed and analyzed later.

One group (control) will be exposed to a 60- to 90-minute conventional theoretical class and the other group (test) will be exposed to the same theoretical class and a 90-minute laboratory class, including exercises and discussions based on the evaluation of a pool of images and extracted teeth. All students will attend the class together before the allocation. For the test group, the participants will be assigned in small groups (7-10 students) mediated by graduate tutors and/or teachers. Students will assess 30 clinical images and 10 teeth for severity (ICDAS scores) and activity status [14]. Tutors/teachers will work on correcting exercises and also discussion of questions raised by the group. In case of disagreement, tooth revaluation will be possible with the help of tutors/teachers so that students understand potential mistakes. For the control group, they will begin the outcomes assessment after having finished the theoretical class.

Despite the allocation, both groups will begin their activities (for training or outcomes assessment) at the same time, avoiding demotivation of any group. Students and teachers/tutors will know the allocated group only when they will be prepared for the activities after the theoretical class, guaranteeing the allocation concealment.

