### Statistical Analysis

For the theoretical evaluation, total number of correct responses for test and control groups will be compared at both times of evaluation (immediate and long term). Data from the number of correct responses per question will be submitted to analysis, also considering the question as a factor.

For the practical assessment, performance-related parameters (sensitivity, specificity, accuracy) when using the visual method for the caries detection and evaluation of lesions activity will be calculated. These values will be compared between groups using multilevel analysis, considering both experimental groups and different centers.

The scores given by students for acceptance and perception of the activities carried out will be compared between groups. Regression analysis will be used in each experimental group to verify the association between student performance in caries lesions detection versus theoretical knowledge and student perception in relation to the activity. Baseline student knowledge and willingness to learn caries detection will be considered during these analyses.

The association between the results of immediate theoretical and practical assessments with knowledge and skills retained in the long term will be assessed.

For all analyses, a multilevel approach will be used to consider different levels explored. The assessment, the student, the center, and the country could be considered as possible levels for these analyses considering the possible clustering observed for centers and, eventually, countries. For all the parameters tested, the influence of the different centers and the level in the course (first or end years) will be investigated by regression analysis. The significance level will be set at 5%.

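### The named model levels omit the tutor-led small group, which exists in the test arm only; a center- or country-intercept model would understate the SE of the immediate arm comparison if outcomes correlate within groups

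*Protocol article*

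**What the plan says.** Experimental Groups (protocol article, Methods) describes a lecture common to both arms: "All students will attend the class together before the allocation". The arms then separate.

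- **Test arm:** "For the test group, the participants will be assigned in small groups (7-10 students) mediated by graduate tutors and/or teachers". Teaching within the group is shared: "Tutors/teachers will work on correcting exercises and also discussion of questions raised by the group".
- **Control arm:** "For the control group, they will begin the outcomes assessment after having finished the theoretical class".

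Statistical Analysis applies one approach throughout: "For all analyses, a multilevel approach will be used to consider different levels explored". The candidate levels are given as follows: "The assessment, the student, the center, and the country could be considered as possible levels for these analyses". The stated reason is "considering the possible clustering observed for centers and, eventually, countries". For the practical assessment the article adds: "These values will be compared between groups using multilevel analysis, considering both experimental groups and different centers".

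The tutor or small group is not named as a level anywhere in the article. The random-effect structure is not given either; in particular, the article does not say whether the arm effect may vary between centers.

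**The concern.** Students in one small group share a tutor, a discussion and the same corrections, so their results after the session may be correlated. Control students have no such grouping. This is a partially nested design: clustering created by the intervention, in one arm only.

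A center or country random intercept does not deal with this. Both arms are present in every center, so a center effect largely cancels from the difference between arms. Tutor-group variation enters one arm only and does not cancel. If the model ignores it, correlated test-arm students are counted as independent.

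At stake are the width of the confidence intervals and the 5% significance level for the immediate randomized comparisons. The long-term comparison is a separate non-randomized phase and is not part of this point.

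**Working it through.** The article states no sample size, power, SD or ICC, so there is no figure of its own to reproduce. The check asks how far the SE would be wrong under a center-intercept model.

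**Inputs from the article**
- Small-group size m = 7 to 10, test arm only (Experimental Groups).
- No grouping of control students after the lecture (Experimental Groups).
- 16 centers (Abstract, Methods).
- Significance level 5% (Statistical Analysis).

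**Assumptions, not in the article**
- Within-group ICC of 0.01 to 0.10.
- 1:1 allocation; the article says only that classes are divided at random into two groups.
- Two-sided tests and equal total variance in the two arms.

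**Formulas**
1. Test-arm design effect: DE = 1 + (m − 1) × ICC. Control-arm design effect: 1.
2. With equal arms, true variance of the difference divided by modelled variance: V = (DE + 1)/2.
3. True SE divided by modelled SE: R = √V.
4. Actual two-sided type I error: 2 × [1 − Φ(1.96/R)].

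Example, m = 7 and ICC = 0.05: DE = 1 + 6 × 0.05 = 1.30; V = 2.30/2 = 1.15; R = √1.15 = 1.072; 1.96/1.072 = 1.828, giving a type I error of 6.8%.

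| ICC (assumed) | m | DE | V | R | Type I error |
|---|---|---|---|---|---|
| 0 | any | 1.00 | 1.000 | 1.000 | 5.00% |
| 0.01 | 7 | 1.06 | 1.030 | 1.015 | 5.35% |
| 0.01 | 10 | 1.09 | 1.045 | 1.022 | 5.52% |
| 0.02 | 7 | 1.12 | 1.060 | 1.030 | 5.70% |
| 0.02 | 10 | 1.18 | 1.090 | 1.044 | 6.05% |
| 0.05 | 7 | 1.30 | 1.150 | 1.072 | 6.76% |
| 0.05 | 10 | 1.45 | 1.225 | 1.107 | 7.66% |
| 0.10 | 7 | 1.60 | 1.300 | 1.140 | 8.56% |
| 0.10 | 10 | 1.90 | 1.450 | 1.204 | 10.36% |

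**Simulation check.** The setting was 16 equal centers, groups of 8, and 1, 2 or 4 groups per center (these counts are assumed), with 4,000 runs per scenario and no true arm effect. Two analyses were compared.

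| ICC | Center intercept only | Arm effect varies by center |
|---|---|---|
| 0 | 5.2-5.6% | 5.0-5.7% |
| 0.02 | 5.2-5.7% | 4.5-4.7% |
| 0.05 | 6.8-7.8% | 4.8-5.2% |
| 0.10 | 9.2-9.5% | 4.7-5.2% |

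The Monte Carlo standard error at 5% is √(0.05 × 0.95/4000), about 0.3 percentage points. The center-intercept results agree with the formula. Letting the arm effect vary by center kept the error close to 5% throughout, without any tutor-group term.

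**The case against.** The strongest reply is that the article fixes no model. The levels are worded as possibilities, nothing rules out a tutor-group term, and a journal article may leave exact random terms to an analysis plan that is not shown. This stands in part: nobody can say from the article that the final model will omit the group. But the article is not silent on clustering. It names the candidate levels and gives the reason for them, and that reason covers centers and countries only. It goes as far out as country and passes over the unit in which the intervention is delivered.

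Second, a reader might infer that every test-versus-control standard error in this trial will be too small. The documents do not support that, for three reasons.

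- It needs a positive within-group correlation, and the article gives none. A single 90-minute session, an image pool common to all centers and staff trained by the principal investigator could keep it low. At an ICC of 0.01-0.02 the effect is minor, and at zero there is none.
- The correlation may differ between theory, practical performance, decision-making and perception, so one value cannot be carried across all outcomes.
- A model in which the arm effect varies by center is compatible with the listed levels and held the error near 5% in the simulation. The article does not state such a term, though, so this protection would rest on an unstated choice. The term also cannot separate tutor-group variation from real differences between centers, and Motivation and Design gives the role of context as a reason for the study.

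Third, Results says that data have already been collected, so adding an ID field will not by itself recover membership for past sessions. This stands, and the fix allows for it.

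**Conclusion.** The point holds in conditional form. The named levels omit the test-arm tutor group, and a model built from them with only center or country intercepts would understate the SE of the immediate arm comparisons in proportion to the within-group correlation. The true SE is about 1.5-4% larger than the modelled one at an ICC of 0.01-0.02, and about 7-20% larger at 0.05-0.10, where the nominal 5% becomes about 7-10%.

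These figures rest on assumed ICCs, 1:1 allocation, two-sided tests and equal total variance. The article does not say how many groups each center has or whether one tutor leads several. If tutors do lead several groups and the correlation comes from the tutor, the effective cluster exceeds 7-10 students and the inflation at a given ICC is larger than shown. It does not follow that every standard error will be wrong: the ICC could be near zero for some outcomes, and the random-effect structure is still open.

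**What to change.** 1. Record the small-group ID and tutor ID for every test-arm student. For sessions already held, retrieve them from local records where possible.
2. In Statistical Analysis, add the small group/tutor (test arm) to the list of levels, and extend the clustering rationale to it.
3. For the immediate comparisons, fit a random small-group effect in the test arm only, with small-sample degrees of freedom (Kenward-Roger or Satterthwaite).
4. Where IDs cannot be recovered, or a center has only one small group so that group and center-by-arm effects cannot be separated, let the arm effect vary by center through a center-by-arm random slope. State this fallback in advance.

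The cost is one extra ID field, some effort to trace past sessions, one additional random term and slightly wider confidence intervals. The teaching procedure does not change.

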### Outcomes Assessment

#### Cost Efficacy

To evaluate the efficacy of the teaching and learning methods both the theoretical knowledge, and the practical skills and clinical decision-making capacity of the students will be evaluated after the theoretical class (control group) and after the theoretical laboratory training (test group).

To evaluate the theoretical knowledge, the students will answer questions about caries lesions detection prepared by professors with expertise in this field. Furthermore, the participants must understand the impact of the correct decision or error when using the ICDAS in clinical practice. The practical assessment will be made through the evaluation of extracted teeth for 1 minute each. Students will evaluate selected tooth surfaces according to the ICDAS criteria with the aid of a light reflector, a plane buccal mirror, and a ballpoint probe. To simulate the distance to observe teeth in the mouth, teeth will be positioned on a plane surface approximately 30 cm from the examiners’ eyes. The teeth will first be examined wet, and then they will be dried for 5 seconds with compressed air. For this evaluation, the students' responses regarding caries severity will be compared with a template made by teachers after visual inspection. To evaluate the capacity of decision making, the undergraduate students should propose the treatment option based on caries lesion detection for 5 clinical cases. Cases were prepared to simulate usual clinical conditions. To assess the cost efficacy of the methods, the efficacy will be considered the number of true answers registered by the students independently on the theoretical and practical tests, as well as in the decision-making query. Direct and indirect costs will be calculated, both individually (the activity itself) and institutionally (to maintain the necessary structure and provide time for the activity). Cost estimation should include planning, preparation of the material, staff training, and implementation of the activity. Lecture and practical activity costing data will be directly collected at all study sites considering institutional information itself. In addition, national databases will be searched to estimate costs of maintenance of universities in each location. Data from these 2 sources will be collated to produce tables of costs for the activity, center, and country.

